## Abstract

**Introduction:**

Motor impairments are highly prevalent in children with Autism Spectrum Disorder (ASD) and have been associated with reduced functional independence, participation, and sociocommunicative development. Despite the growing body of evidence supporting the relevance of motor functioning in ASD, motor-based interventions remain underrepresented in high-quality randomized clinical trials. The Global Integration Method (Método de Integração Global - MIG) is an intensive, interdisciplinary intervention grounded in the theories of predictive coding and embodied cognition, with emphasis on motor organization, proprioceptive stimulation, and generalization of functional skills in real-life contexts.

**Objective:**

The aim of this study is to evaluate the effectiveness of the MIG program in improving fundamental motor skills and achieving functional goals, compared with conventional physiotherapy and psychological interventions, in children with ASD. Secondary objectives are to investigate the effects of MIG on balance, sociocommunicative skills, and motor performance.

**Methods and analysis:**

This is a three-arm randomized controlled trial with concealed allocation and blinded outcome assessors. Sixty-six children with ASD, aged 6 to 12 years, classified as requiring level 1 or 2 support, will be randomized into one of three groups: (I) MIG program, (II) conventional psychological intervention, and (III) conventional motor physiotherapy. Interventions will last five weeks. Assessments will be conducted at baseline, immediately post-intervention, and three months after completion. Primary outcomes include fundamental motor skills and functional goal attainment. Secondary outcomes include measures of balance, sociocommunicative skills, and motor performance. Data will be analyzed using linear mixed-effects models, following the intention-to-treat principle.

**Ethics and dissemination:**

The protocol was approved by the Research Ethics Committee of the Faculty of Medical Sciences of Minas Gerais, Brazil (Approval No. 7,456,658). Written informed consent will be obtained from parents or legal guardians, and assent will be sought from participating children when developmentally appropriate. Study findings will be disseminated through peer-reviewed publications, conference presentations, and reports to participating families and institutions.

**Clinical Trial Registration:**

This protocol was prospectively registered in the Brazilian Registry of Clinical Trials https://ensaiosclinicos.gov.br/rg/RBR-7r6n8zd, identifier U1111-1326-2272.

## Introduction

1

Autism Spectrum Disorder (ASD) is a neurodevelopmental condition defined by impairments in social communication and the presence of restricted and repetitive patterns of behavior (1). Although diagnostic criteria predominantly emphasize sociocommunicative aspects, a growing body of evidence indicates that motor impairments are widely observed characteristics in this population (2–6).

In one of the largest population-based studies on motor skills in ASD, Bhat found that approximately 88% of 13,528 children in the United States were at high risk for motor impairment. Despite this striking figure, only 32% of the children received physiotherapy and 13% participated in motor-based therapeutic activities, highlighting a substantial discrepancy between the prevalence of impairments and access to interventions (6). Licari et al. analyzed data from 2,084 Australian children diagnosed by six years of age and observed that motor difficulties are common yet underrecognized in clinical practice. The study found that 35.4% had clinically significant motor deficits and 43.7% showed moderately below-average performance, totaling nearly 80% with some level of motor impairment (2).

Motor impairments described in the literature include difficulties in fine and gross motor coordination, balance, motor planning, postural control, and manual dexterity—skills that are essential for autonomy and participation in school, social, and family activities (4). Evidence indicates that these deficits may emerge in the first years of life, even preceding sociocommunicative symptoms (7), and tend to persist across development, with cumulative effects on functionality and quality of life (8).

The Global Integration Method (Método de Integração Global - MIG) represents an innovative, intensive, and interdisciplinary intervention approach for children and adolescents with ASD (9). Unlike traditional approaches that fragment development into predominantly cognitive, behavioral, or linguistic components, MIG is based on the premise that motor function, proprioception, and bodily organization constitute foundational processes for the emergence of communication, social interaction, and functional participation in everyday life (9).

Operationally, MIG is organized into intensive interdisciplinary programs, with a monthly workload ranging from 60 to 80 h, distributed among different professionals according to functional priorities jointly defined with the family (9). Interventions take place in highly structured environments known as City of Tomorrow (Cidade do Amanhã), which replicate natural daily-life contexts such as home, school, supermarkets, and other community settings (10). In this way, training occurs in environments that simulate real life, promoting the immediate generalization of skills to contexts of greatest relevance to the child or adolescent and their family (11).

MIG is grounded in two major contemporary theoretical frameworks. The first is predictive coding theory, according to which the brain continuously operates by generating hypotheses about the environment and comparing them with incoming sensory information. In recent years, there has been a substantial increase in studies identifying predictive coding as one of the most robust and parsimonious explanations for typical and atypical brain functioning (12–14). In the case of ASD, there is consistent evidence that children and adolescents experience difficulties integrating sensory, motor, and social cues, which compromises their ability to form stable predictions about the environment and to update those predictions efficiently (15, 16).

The second theoretical foundation is embodied cognition, according to which complex cognitive and sociocommunicative processes do not develop independently of the body, but rather emerge in close integration with motor experiences, bodily sensations, and actions in the environment. The literature has shown that movement patterns, postural stability, coordination, rhythm, and active exploration directly influence the development of communicative and social competencies from the earliest years of life (17, 18). This perspective challenges traditional views that treat language, social interaction, and motor function as independent domains, instead suggesting that these systems are organized in a mutually dependent manner.

One of the central components of MIG, directly aligned with the principles of predictive coding and embodied cognition, is the use of the MIG Flex therapeutic suit, an exoskeleton developed based on the mapping of myofascial lines and designed to provide continuous proprioceptive stimulation, postural support, and bodily organization (9). By stabilizing the trunk and aligning body segments, the suit promotes more consistent bodily signals, thereby reducing the amount of prediction error generated by the organism. This sensorimotor stability increases the predictability of bodily experiences, helping the child better anticipate the consequences of their movements and organize actions more efficiently.

Another distinguishing feature of MIG is the systematic integration of cognitive, behavioral, and structured teaching strategies organized through narrative grammar (9). The literature consistently demonstrates the effectiveness of cognitive and behavioral techniques in enhancing adaptive skills, promoting functional communication, and developing social repertoires in children with ASD (19, 20). In parallel, narrative grammar—understood as a cognitive schema that organizes events into comprehensible structures with characters, intentions, actions, and consequences—has been shown to be a promising resource in interventions for individuals with ASD, as it provides predictability, temporal coherence, and support for processing complex social information (21).

In addition, MIG adopts a family-centered therapeutic planning model, in which goals are collaboratively defined and based on real functional needs within daily routines (10, 22). This alignment between intervention and everyday life increases the practical relevance of the program and strengthens adherence, ensuring that the skills developed have immediate utility in contexts of greatest importance to the child and their caregivers.

Despite growing evidence indicating that motor impairments are highly prevalent in ASD and influence sociocommunicative development, a significant gap remains in clinical practice, which the MIG protocol seeks to address. The effects of MIG have been investigated in children and adolescents with ASD and indicate that the intervention promotes meaningful functional improvements when assessed through parent-reported outcomes and measures sensitive to change (10, 11, 22). *Although no previous feasibility studies have been conducted, pre- and post-intervention studies indicate that children and their families are able to attend and complete most of the sessions required by this intensive program, suggesting good feasibility and adherence* (10, 11, 22)*.* Taken together, these studies suggest that MIG is a promising intervention capable of producing functional, communicative, and motor improvements, with strong family acceptance and alignment with contemporary family-centered care guidelines. However, MIG has not yet been evaluated in randomized controlled trials. Therefore, it is necessary to conduct a study that evaluates the potential effects of MIG when compared with conventional interventions.

## Objectives

2

This study aims to evaluate the effectiveness of the MIG program for children and adolescents with ASD in improving fundamental motor skills (capacity) and in achieving functional goals, compared with conventional treatments (psychology based on cognitive and behavioral techniques and Applied Behavior Analysis, and motor physiotherapy). As a secondary objective, this study seeks to verify the effectiveness of the MIG program on balance, sociocommunicative skills, and motor skills (performance).

## Methods

3

### Design

3.1

This study is a three-arm, single-blind randomized controlled trial designed to compare the Global Integration Method (MIG) program with conventional physiotherapy and conventional psychological interventions. Participants will be randomly allocated to one of three groups, with concealed allocation and blinded outcome assessors. Assessments will be conducted at three time points: baseline, immediately after the intervention period, and three months after intervention completion. The trial protocol was developed in accordance with the Standard Protocol Items: Recommendations for Interventional Trials (SPIRIT) guidelines (23).

### Patient and public involvement (PPI)

3.2

Patients and the public were not involved in the design of the study or in the definition of research questions and outcome measures. However, to ensure that the perspectives of healthcare professionals and families are integrated into the study, a monitoring committee will be established. This group will consist of a clinical specialist and a family representative (a caregiver of a child with ASD), acting in an advisory capacity during the analysis and interpretation of the results. Their contribution is expected to enrich the discussion by integrating technical expertise with practical, real-world perspectives, helping to ensure that the final conclusions are both clinically meaningful and socially relevant.

### Setting

3.3

This study will be conducted at two distinct sites. MIG program sessions will take place at the Reabilitar Clinic, within the “Cidade do Amanhã” (City of Tomorrow) facility, located in Ribeirão das Neves, Minas Gerais, Brazil. Conventional physiotherapy and psychology sessions will be conducted in the standard treatment rooms of the Reabilitar Clinic.

### Participants

3.4

The study sample will be recruited by convenience from public institutions, philanthropic organizations, and private physiotherapy facilities located in the municipality of Ribeirão das Neves, Minas Gerais, Brazil. Children aged 6 to 12 years at the start of the intervention, with a confirmed diagnosis of Autism Spectrum Disorder (ASD) and classified as requiring level 1 or 2 support, will be included. Participants presenting cognitive, behavioral, or clinical comorbidities that may interfere with adequate comprehension of instructions or with the safe performance of the tasks included in the proposed intervention program will be excluded.

### Sample size

3.5

The sample size was set at 66 participants, distributed into three groups with 22 individuals in each group. Sample size determination was based on the findings of a previous investigation that analyzed the effects of the MIG program in children with ASD (10). The calculation considered an effect size of 0.87, derived from outcomes of the Canadian Occupational Performance Measure, a statistical power of 80%, a significance level of *α* = 5%, and an estimated attrition rate of 20% over time. The calculation was performed using G*Power software version 3.1 (24).

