### Data analysis

3.10

Analyses will be performed using IBM SPSS Statistics software. Descriptive analyses will initially be used to characterize the sample in terms of age, sex, and level of support. Data distribution will be assessed using the Shapiro–Wilk test. Baseline group comparisons will be conducted using one-way analysis of variance (ANOVA) or Kruskal–Wallis tests, as appropriate. All analyses will follow the intention-to-treat principle. Linear mixed-effects models will be used to evaluate intervention effects over time, including group-by-time interaction terms. In the presence of significant interactions, *post hoc* analyses with Bonferroni correction will be performed. Missing data will be handled using maximum likelihood estimation within the mixed-effects models. A two-sided significance level of 5% (*p* < 0.05) will be adopted for all analyses.

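### Section 3.5: on a two-sided t-test reading, 22 children per arm is the number needed before dropout, so with 20% attrition the power is about 71%, not 80%

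*Protocol article*

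**What the plan says.** Section 3.5 (Sample size) fixes the number: "The sample size was set at 66 participants, distributed into three groups with 22 individuals in each group". The inputs it lists are "an effect size of 0.87, derived from outcomes of the Canadian Occupational Performance Measure", power of 80%, alpha of 5% and "an estimated attrition rate of 20% over time". On the software it says: "The calculation was performed using G*Power software version 3.1". It does not say which test was entered, whether 0.87 is a standardised difference between two arms or some other effect measure, or whether the test was one- or two-sided. It gives one sample size, not one before and one after attrition.

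Section 3.10 (Data analysis) sets a two-sided 5% level for all analyses. It plans linear mixed models with a group-by-time interaction, maximum likelihood for missing data, and Bonferroni-corrected post hoc comparisons when the interaction is significant. It does not say how many comparisons are corrected.

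**The concern.** A reader of section 3.5 will take 22 per arm as a number that already absorbs 20% loss and still leaves 80% power. On the simplest reading of the listed inputs, 22 is instead the number needed when nobody is lost. The stated power would then belong to a trial with complete follow-up, not to the one described.

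What is at stake is how the result is read. A null finding for MIG against either comparator would be taken as coming from a trial with 80% power after dropout, when the power for a plain pairwise contrast may be nearer 70%, and lower after the multiplicity correction.

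**Working it through.** **Inputs.** From section 3.5: effect size 0.87, power 80%, alpha 5%, attrition 20%, 22 per arm. From section 3.10: two-sided. Assumed, because the article does not say: a two-sample t-test with 0.87 as Cohen's d between two arms.

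**Formula.** With n evaluable per arm, the test statistic is noncentral t with 2n − 2 degrees of freedom and noncentrality d × √(n/2). Two-sided power is the probability that it falls outside ± the 97.5% point of the central t.

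**Step 1: reproduce the plan's figure without attrition.**
- n = 21: noncentrality 0.87 × √10.5 = 2.82, power 78.5%.
- n = 22: noncentrality 0.87 × √11 = 2.89, critical value 2.02, power 80.5%.

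So 22 is the smallest number per arm that reaches 80%, and 3 × 22 = 66. The match is exact, with no allowance for loss.

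**Step 2: add the attrition.** 22 / (1 − 0.20) = 27.5, so 28 per arm and 84 in total. The looser 22 × 1.2 = 26.4 gives 27 per arm and 81. Neither gives 66.

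**Step 3: power at 66 randomised with 20% lost.** 22 × 0.8 = 17.6 per arm, about 53 in all.
- n = 17.6: noncentrality 0.87 × √8.8 = 2.58, power 70.7% (69.1% at 17, 71.8% at 18).
- The effect detectable with 80% power at 17.6 per arm is d = 0.97.

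**Step 4: other routes to 66.**

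| Reading | Before attrition | After 20% attrition |
|---|---|---|
| One-sided 5% t-test, d = 0.87 | 18 per arm | 18 × 1.2 = 21.6, so 22; 18/0.8 = 22.5, so 23 |
| One-way ANOVA, one arm 0.87 SD above two equal arms (f = 0.41) | 63 total | 79 total |
| One-way ANOVA, f = 0.435 | 57 total | 72 total |
| One-way ANOVA, f = 0.87 | 18 total | 23 total |
| Repeated-measures ANOVA, correlation 0.5 assumed | at most 39 total | at most 49 total |
| Two-sided contrast adjusted for baseline, correlation 0.5 assumed | 17 per arm (power 81%) | 17/0.8 = 21.25, so 22 |

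Two of these give 22 per arm with attrition included: the one-sided test with the looser inflation, and the baseline-adjusted contrast at a correlation of 0.5.

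**Step 5: power if the contrast is adjusted for baseline.** Adjustment divides the residual SD by a factor that raises the effective effect to 0.87/√(1 − r²), with 2n − 3 degrees of freedom. At 17.6 per arm and two-sided 5%:

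| Assumed baseline-outcome correlation r | Power |
|---|---|
| 0.30 | 75% |
| 0.40 | 78% |
| 0.45 | 80% |
| 0.50 | 82% |
| 0.60 | 88% |

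**Step 6: Bonferroni.** Unadjusted t-test, 17.6 per arm, d = 0.87. If the two contrasts of MIG with its comparators are corrected (alpha 0.025), power is about 60%. If all three pairs are corrected (alpha 0.0167), it is about 53%. The number of comparisons is an assumption in both.

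**The case against.** The strongest reply is that the t-test is the reviewer's choice, not the plan's. Section 3.10 plans a mixed model that uses the baseline visit and partial data, and step 4 shows that a two-sided baseline-adjusted contrast at a correlation of 0.5 leads to 22 per arm with attrition correctly included. That stands, and it rules out the claim that no two-sided reading yields 66 with 20% attrition. It does not rescue section 3.5 as written, because that route needs a correlation the article does not state.

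A reader might also infer that attrition was certainly forgotten. The documents do not prove this. A one-sided calculation, 18 × 1.2 = 21.6, would also give 22, and then attrition was applied but the sidedness was wrong. Omitted attrition is the better fit, because the no-dropout match is exact while the one-sided route needs the looser inflation formula and conflicts with section 3.10. Either way, power for the unadjusted two-sided contrast after 20% loss is about 71%.

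Finally, a condensed article may leave the G*Power settings to the full protocol. That is fair, and the missing settings are not the point here. The point is that the figures printed together do not agree under the natural reading.

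**Conclusion.** The point holds in a conditional form. Read as a two-sided 5% two-arm t-test at d = 0.87, section 3.5 gives the number required with no dropout; 20% attrition would need 28 per arm (84). With 66 randomised and 20% lost, power for an unadjusted pairwise contrast on completers is about 71% instead of 80%.

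It would go too far to say that the trial's power is 71%. That figure belongs to one analysis. For the planned model, power cannot be determined from the article: it runs from about 75% to 88% for assumed correlations of 0.3 to 0.6, before any Bonferroni correction. It would equally go too far to quote 53% as the power after correction, since section 3.10 does not fix the number of comparisons, and the objectives, which set MIG against the conventional treatments, would also fit two contrasts (about 60%).

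**What to change.** Correct section 3.5 as follows.

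- Show N before and after attrition, with the test and effect-size type behind 0.87, and make the sidedness agree with section 3.10.
- State that 66 randomised leaves about 53 evaluable at 20% loss, with about 71% power for an unadjusted two-sided 5% pairwise contrast at d = 0.87, and 80% power only from d of about 0.97.
- Alternatively, if the 80% is meant for the baseline-adjusted mixed-model contrast, say so and give the assumed baseline-outcome correlation with its justification. At 17.6 per arm it must be about 0.45 or higher.
- State the number of comparisons that the Bonferroni correction in section 3.10 covers, and that power is lower after it.

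The cost is wording and a less favourable stated power. No extra children are needed and the analysis does not change.

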#### MIG program

3.7.1

Participants in this group will receive a protocol specifically structured to assess the motor component of the MIG program. The intervention will be delivered by physiotherapists with prior experience in MIG and additional training provided by an interdisciplinary team (psychologists, speech-language pathologists, and occupational therapists), ensuring standardization of the research protocol implementation. The motor component will be delivered in three weekly sessions, each lasting 50 min, over a period of five weeks, following a previously defined structure. *Although the MIG is conceived as an intensive interdisciplinary program, the present trial was designed to isolate and evaluate only its motor component; therefore, the dosage reported here refers exclusively to the physical therapy sessions and does not correspond to the total interdisciplinary workload of the complete MIG protocol.*

In all sessions of the motor component protocol of the MIG program, the child will wear the MIG Flex therapeutic suit. This suit provides proprioceptive input and postural support during motor activities. This resource serves a dual function by promoting bodily stability and improved motor organization, while reducing the cognitive load required for postural maintenance and movement coordination, thereby freeing attentional and cognitive resources that can be directed toward interaction, play, and communication. At the beginning of each session, the physiotherapist will place and adjust the MIG Flex on the child and then initiate the narrative designed for that session. The narrative will introduce the main character, the setting, and the temporal context (initial situation), as well as the problem, triggering event, or central challenge (initiating event). The character's feelings or emotions and the plan for problem resolution will also be explicitly presented; this plan will correspond directly to the motor activities the child must perform to “help” the character, together with psychoeducational components about emotions aimed at promoting generalization of concepts and strengthening cognitive flexibility by allowing the participant to recognize common principles across different symbolic situations. The narratives used in sessions 01 and 15 are described in Supplementary Material 1.

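### The planning effect of 0.87 is very probably a pre-post change used as a between-arm difference, so the stated 80% power is not supported for MIG against active comparators, physiotherapy above all

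*Protocol article*

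**What the plan says.** Protocol article, section 3.5 (Sample size), sets 66 children, 22 in each of three arms, and bases this on reference 10, an earlier study of MIG in children with ASD. It states: "The calculation considered an effect size of 0.87, derived from outcomes of the Canadian Occupational Performance Measure, a statistical power of 80" per cent, with alpha 5% and 20% attrition. It names G*Power but not the test, the effect-size metric or the contrast.

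Section 1 (Introduction) cites references 10, 11 and 22 together in this remark: "pre- and post-intervention studies indicate that children and their families are able to attend and complete most of the sessions". It then says: "However, MIG has not yet been evaluated in randomized controlled trials".

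The trial compares MIG with two active treatments. The physiotherapy arm (3.7.3) receives 20 minutes of motor skills training, 10 of balance and 10 of ball activities in each session. The psychology arm (3.7.2) does not directly address motor training or motor goals. Section 3.10 plans linear mixed models with group-by-time terms, Bonferroni-corrected post hoc tests and a two-sided 5% level.

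On the intervention, section 3.7.1 says that the trial isolates the motor component of MIG and that the dosage "does not correspond to the total interdisciplinary workload of the complete MIG protocol".

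**The concern.** A pre-post effect measures how much a treated group changes. It includes the treatment effect, but also maturation, regression to the mean, familiarity with the interview and parental expectation. A randomised comparison estimates what is left after the comparator's own change has been subtracted. If 0.87 is a pre-post effect and was entered as the difference between arms, the calculation assumes that the comparator arms do not change on COPM.

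That is hard to accept for physiotherapy, which also trains motor skills. COPM is rated through parent interviews (3.8.1, 3.9) and families are not blinded (3.6), so expectation can move scores in any arm. The source effect also concerns the MIG program, while this trial tests only its motor component, and section 3.5 offers no argument for carrying the value over.

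At stake is the power statement for the trial's main question. A reader would take 80% as the chance of detecting an advantage of MIG over conventional therapy, when the figure may describe something else.

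**Working it through.** **Inputs from the protocol.** Effect size 0.87, power 80%, alpha 5%, attrition 20%, 22 per arm (3.5); two-sided testing (3.10). Evaluable children after 20% loss: 22 × 0.8 = 17.6 per arm.

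**Step 1: reproduce 22 per arm.** For a two-sample t-test, the noncentrality is d × √(n/2) with 2n − 2 degrees of freedom.
- n = 22: 0.87 × √11 = 2.885, 42 df, two-sided power 80.5%.
- n = 21: power 78.5%.

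So 22 is the smallest n that reaches 80%, before any attrition. Adding 20% attrition gives 22 / 0.8 = 27.5, that is 28 per arm.

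**Step 2: try the alternatives.**
- Paired pre-post test, noncentrality d × √n: n = 12 gives 78.3% and n = 13 gives 82.1%. The requirement is 13, or 17 with attrition.
- Three-group ANOVA: f = 0.87 needs 18 in total (23 with attrition); f = 0.435 needs 57 (72 with attrition). Neither gives 66.
- One-sided two-sample test with attrition: normal approximation 17 / 0.8 = 21.25, so 22; t-test 18 × 1.2 = 21.6, so 22, or 18 / 0.8 = 22.5, so 23.

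Every variant found that reaches about 22 per arm is a two-sample comparison. The only two-sided one leaves attrition out.

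**Step 3: what a changing comparator does.** The protocol gives no between-arm effect, so this is an illustration. Assume that 0.87 is MIG's own standardised change, that the comparator achieves a share c of it, and that the SD is the same in both arms. Then d = 0.87 × (1 − c).
- c = 1/3: d = 0.58. Noncentrality is 0.58 × √11 = 1.924 (n = 22) or 0.58 × √8.8 = 1.721 (n = 17.6).
- c = 1/2: d = 0.435. Noncentrality is 0.435 × √11 = 1.443 or 0.435 × √8.8 = 1.290.

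**Step 4: allow for baseline adjustment.** If 0.87 is scaled to the raw SD, adjusting for baseline with correlation ρ gives an effective d of d / √(1 − ρ²). The values ρ = 0.5 and 0.7 are assumed. For d = 0.58 this gives 0.670 and 0.812; for d = 0.435 it gives 0.502 and 0.609.

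Power, two-sided 5%, before Bonferroni correction:

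| Comparator share | d | Unadjusted, n = 22 | Unadjusted, n = 17.6 | Adjusted, n = 22 | Adjusted, n = 17.6 |
|---|---|---|---|---|---|
| none | 0.87 | 80% | 71% | not needed | not needed |
| one third | 0.58 | 47% | 39% | 58–75% | 49–65% |
| one half | 0.435 | 29% | 24% | 37–51% | 30–42% |

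**Step 5: what the fixed sample can detect.** Solving the Step 1 formula for 80% power gives d = 0.865 at n = 22 and d = 0.973 at n = 17.6, that is about 0.87 and 0.97.

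**The case against.** Several parts of the opposing case stand.

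- **The within-group reading is an inference.** Reference 10 is not at hand. The pre-post description comes in a remark on attendance that covers three references. The lack of a randomised trial does not exclude a non-randomised comparison group. A reader might infer that 0.87 is certainly an uncontrolled change; the protocol makes this very probable but does not say it.
- **The test is not named.** Use as a between-arm difference is inferred from the match in Steps 1 and 2.
- **The two comparators differ.** Psychology does not target motor goals, so little COPM change on such goals is plausible there. The argument bears mainly on physiotherapy.
- **The unadjusted figures may be pessimistic.** The planned mixed models use the baseline measurement. If 0.87 is scaled to the raw SD, Step 4 applies. If it is already scaled to the SD of change, that gain disappears. The protocol does not say which. A smaller share combined with a high correlation can reach 80%: at one quarter, d = 0.6525, and with ρ = 0.7 the effective d is 0.914 and power is 84% with 22 per arm (75% with 17.6).

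Two stronger readings should not be drawn. One compares this trial's hours with the Introduction's figure, "with a monthly workload ranging from 60 to 80 h". That figure describes MIG in general and nothing ties it to the study behind 0.87, so a dose ratio has no basis. The other faults section 3.5 for giving no planning value for TGMD-2, which a condensed article may leave to the full protocol.

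None of this supplies a reason to treat 0.87 as a difference from active therapy.

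**Conclusion.** The concern holds in this form: the stated 80% is not supported as the power for MIG against active comparators. It rests on two strong inferences, that 0.87 is a pre-post change and that it was entered in a two-sample calculation.

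The size of the shortfall is unknown, because it depends on the comparator's change, the SD behind 0.87 and the baseline correlation. With 22 per arm, a comparator achieving one third to one half of MIG's gain leaves unadjusted power of 47% to 29%. Baseline adjustment at the assumed correlations gives between 37% and 75% over the same range. In these scenarios power stays below 80%, and attrition lowers it further.

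A reader might infer that the trial has some particular low power, such as 29%. The protocol does not support that, since the comparator shares are assumptions. Nor does the point invalidate the randomisation or the planned analysis. It concerns the justification of the sample size and how the power claim may be read, chiefly for MIG against physiotherapy.

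**What to change.** In section 3.5:

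1. State the test, the effect-size metric and the contrast behind 0.87. If it is a pre-post COPM effect of the MIG program, label it so, and note that this trial tests only the motor component.
2. Withdraw 80% as the power for MIG against the active comparators.
3. Give instead the standardised between-arm difference that 22 per arm can detect with 80% power at two-sided 5%: about 0.87 with no loss and about 0.97 with 20% loss, before Bonferroni correction.
4. Add that power against physiotherapy is lower than a calculation on 0.87 implies if that arm also improves.

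The sample size stays at 66. The cost is a less favourable power statement.
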